### Indemnity

This study is not an intervention study and poses a low risk to participants. For some attendees, the test results may indicate a deviation in cognitive abilities, which suggests early cognitive decline. When this occurs, we provide a comprehensive medical consultation with the study’s clinical investigator to ensure further medical care and possibly determine a further diagnostic plan. Participants may report slight fatigue when participating in the different assessments. A short preventive break is taken after approximately half of the testing procedure.

Part of the screening procedure involves wearing a head-mounted display with VR, which may cause cybersickness [29]. Cybersickness is triggered by visual stimuli during exposure to the virtual environment and shares similar symptoms with motion sickness, including nausea, sweating, dizziness, and fatigue. To minimize the risk of cybersickness, the participants undergo screening in a static (sitting or standing) position. The participants could withdraw from the screening in case of cybersickness. Except for these considerations, no health risks or side effects are expected for the participants.

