### Study Procedure

At the beginning of the study, the investigator clarifies in detail the screening procedure and COVID-19–related hygiene measures and obtains signed written informed consent from the volunteers. The screening procedure for each participant consists of 3 blocks (see Figure 1). Anthropometric, sociodemographic, and risk factor data are collected in the first block (A). The Brief Smell Identification Test (B-SIT) [23], Food Frequency Index (FFI) [30], and Dementia Detection Test (DemTect) are also performed in block A using a laptop computer as well as pen and paper. The Dual-Task Assessment (DTA) [25,31,32], Trail-Making Test (TMT) [33], Reaction Time Test “Match 4 Point Test” [34], and Erlangen Test of Activities of Daily Living in Persons With Mild Dementia or Mild Cognitive Impairment (ETAM; parts transport and finances) [34] are performed in the second block (block B) using software as well as pen and paper. The same assessments from block B are performed in the third block (block C) using MR technologies, tailor-made MR software, and suitable AR and VR hardware. Prior randomization determines the order in which participants perform blocks B and C.

The entire testing procedure lasts approximately 130 minutes, including a 10-minute break between blocks B and C. Trained project staff conduct the study. A medical doctor acting as the clinical investigator is available to the participants for consultation to answer questions related to their cognitive health.

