### Outcome Parameters and Data Analysis

Statistical analyses will be performed to identify possible correlations between the different components of the MST and MR-enhanced MST. Spearman rank correlations (Spearman ρ) or product-moment correlations (Pearson correlations) will be calculated, depending on the distribution of the collected data. Multiple regression analyses will be conducted for cases of strong effects in the correlation between the MST and MR-enhanced MST. Descriptive statistics of the data will be presented as means and SDs. The level of significance is set at α=.05. The statistical data will be evaluated using SPSS (IBM Corp).

For usability assessment, usability experts will collect and analyze data from the video observations and questionnaires. The video observations will be evaluated using “Eisenhower's Urgent/Important Principle” [78]**,** in which items are classified as “not urgent” to “urgent” and as “not important” to “important.” The “urgent” and “important” items indicate higher needs of improvement. The questionnaires addressing the personal experiences with the screening procedure are based on a 5-point Likert scale, where 1 indicates “very good usability.”

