## Results

This study was funded by the Austrian Research Promotion Agency (FFG, grant 866873) and was approved by the ethics committee of the Medical University of Graz, Austria. The funding body and funding source are not involved in performing the research and do not play any role in the execution of the study, data analyses, or result interpretation. All described procedures related to the equipment and software development, preliminary tests, study organization, and recruitment plans were completed. The investigators involved in the test procedure were trained to use the MR prototype and perform the entire screening procedure in joint and separate sessions. As of July 15, 2022, a total of 70 participants have been screened. Because this study describes the protocol for the implementation of the MR-enhanced multimodal screening tool, no results are currently available. Data analyses and result dissemination will be completed by September 2023.

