### Strengths and Limitations

We designed this study to compare the results of the MST (block B) to those of the MR-MST (block C). The performance in the first block may facilitate the performance in the second block. To minimize the “learning effect,” these blocks were randomized among participants. As the entire screening procedure has a duration of approximately 130 minutes, participants may experience cognitive fatigue, which could influence the results of the tests. The effect of possible cognitive fatigue was minimized by providing a resting break between the blocks and frequently obtaining feedback from participants. The order of assessments in blocks B and C was selected to ensure maximum convenience and time efficiency when changing from assessments performed using AR to those performed using VR in block C.

Another limitation of this study protocol is related to the fact that the experiments are performed at different times of the day (eg, in the morning and afternoon) and by different investigators. To reduce the impact of circadian rhythms on cognitive performance, we avoided testing in the early morning and late afternoon. To ensure standard testing conditions, all involved investigators obtained the same training using the AR and VR technologies and performed the screening procedure.

One strength of this study is that the assessments performed with VR included familiar situations and daily life activities (eg, crossing a street, shopping in a grocery store) in which immersion into the virtual world created a cognitive experience that aligned with real-life demands. The MR-enhanced assessments were designed to resemble the assessments performed with pen and paper as much as possible. We are aware that the results of MR-enhanced MST may not be directly comparable to those of the MST because of the specificity of the AR and VR equipment and environment. These findings will shed more light on the extent, art, and origin of possible differences, which will enable further adaptations and optimizations of the prototype.

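### The MST to MR-MST correlations are stated without a term for block order, and randomising the order does not remove order shifts from a pooled correlation

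*Protocol article*

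**What the plan says.** Study Procedure has the dual-task walk, the Trail-Making Test, the reaction time test and two ETAM parts done conventionally in block B and again with mixed reality in block C. On sequence and timing it states: "Prior randomization determines the order in which participants perform blocks B and C". And: "The entire testing procedure lasts approximately 130 minutes, including a 10-minute break between blocks B and C".

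Strengths and Limitations acknowledges an order effect: "The performance in the first block may facilitate the performance in the second block". The remedy named for this learning effect is that "these blocks were randomized among participants". Cognitive fatigue is also named as a possible influence, countered by a rest break and participant feedback.

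Outcome Parameters and Data Analysis gives the comparison: "Statistical analyses will be performed to identify possible correlations between the different components of the MST and MR-enhanced MST". The coefficient is Pearson or Spearman, depending on the distribution. The next step is conditional: "Multiple regression analyses will be conducted for cases of strong effects in the correlation between the MST and MR-enhanced MST". No order term is mentioned for the correlations, and the regression predictors are not named.

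**The concern.** The safeguard fits a different analysis from the one stated. Randomised order protects a comparison of block means, because learning and fatigue fall equally on B and C on average. The stated comparison is a correlation over all participants. In one order block B carries the second-block shift; in the other order block C does. Order therefore adds spread to both scores. If both blocks shift the same way, it also pushes the two scores apart within each person.

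The correlation is the stated measure of how the two versions relate, and its strength decides which pairs go on to regression. If order lowers it, agreement is understated, and part of the shortfall could be put down to the mixed-reality equipment when it comes from test order. A later regression that included order could not recover a pair already set aside on an unadjusted correlation.

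**Working it through.** **Inputs from the protocol article.** Study Design, Participants, and Recruitment Procedure gives effect size 0.35, α=.05, a value of .95 labelled β, and about 100 participants. Order is randomised.

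**Assumptions.** The effect size is a correlation (no metric is named). The .95 is power. Allocation to the two orders is 1:1 (not stated). Second-block shifts are additive, in units of the within-order SD. No order-effect size is given, so a range is shown.

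**The plan's sample size.** Fisher z, two-sided: n = ((1.960 + 1.645)/atanh(0.35))² + 3 = (3.605/0.3654)² + 3 = 100.3, so 101. This matches about 100. A paired mean difference of 0.35 SD would need 107 (normal approximation) or 109 (exact t), so the correlation reading fits best. Power at n=100 is Φ(0.3654·√97 − 1.960) = Φ(1.639) = 0.949.

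**Effect of order on a pooled correlation.** Let X = 1 if block B is second and 0 otherwise. Then Var(X) = 1/4. Block B gains dB·X and block C gains dC·(1 − X). With within-order correlation ρ:

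- Var(B) = 1 + dB²/4 and Var(C) = 1 + dC²/4
- Cov(B,C) = ρ − dB·dC/4
- pooled r = (ρ − dB·dC/4) / √[(1 + dB²/4)(1 + dC²/4)]

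For an equal shift d, each variance rises by d²/4 and the covariance falls by d²/4.

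**Results for ρ = 0.35, n = 100.**

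| dB / dC (SD) | Calculation | Pooled r | Power |
|---|---|---|---|
| 0 / 0 | – | 0.350 | 0.949 |
| 0.2 / 0.2 | 0.3400/1.0100 | 0.337 | 0.932 |
| 0.3 / 0.3 | 0.3275/1.0225 | 0.320 | 0.905 |
| 0.5 / 0.5 | 0.2875/1.0625 | 0.271 | 0.780 |
| 0.5 / 0 | 0.35/√1.0625 | 0.340 | 0.936 |
| −0.2 / +0.3 | 0.365/√(1.0100·1.0225) | 0.359 | 0.959 |

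A within-order correlation of 0.80 becomes 0.782, 0.760 or 0.694 for equal shifts of 0.2, 0.3 or 0.5 SD.

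**Against sampling error.** The SE of r at n=100 is about (1 − 0.35²)/√99 = 0.088. The bias is 0.013 (0.15 SE) at 0.2 SD, 0.030 (0.34 SE) at 0.3 SD and 0.079 (0.90 SE) at 0.5 SD.

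**Does adjustment work?** In a simulation with 10,000 runs, n=100 and 0.5 SD in both blocks, the pooled correlation averaged 0.268 with power 0.784. The order-adjusted correlation averaged 0.349 with power 0.951. On ranks, the mean rose from about 0.25 to about 0.33, so the adjustment also serves the Spearman route.

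**Price if there is no order effect.** Power of the partial correlation is Φ(0.3654·√96 − 1.960) = 0.947, against 0.949.

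**The case against.** The best case against the point is that it rests on silence in a condensed article. The analysis paragraph is short, the regression predictors are unnamed, and a full plan may already adjust for order. The article also claims only to minimise the learning effect, not to remove it. That is fair: nothing here shows that the final analysis will omit order. The point survives as an improvement because the article names both the analysis and the safeguard, and that safeguard does not act on a pooled correlation.

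The second objection is size, and it largely stands. At 0.2 to 0.3 SD the bias is at most about a third of a standard error. Equal shifts in both blocks may also be unlikely. Participants come from the earlier project phase, in which the MST was tested, so practice gains on the conventional tests could be smaller than on the new versions. Learning and fatigue also pull in opposite directions. If only one block shifts, little is lost.

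Two stronger readings are tempting, and the documents do not support them. A reader might infer that the reported correlations will be materially too low. No order-effect size is given, the sign of the bias depends on the pattern of shifts, and no cut-off for a strong correlation is stated, so no pair can be shown to miss regression. A reader might also infer that VR after-effects contaminate block B when C comes first, since Indemnity says cybersickness "shares similar symptoms with motion sickness, including nausea, sweating, dizziness, and fatigue". No frequency or duration is given, the same section provides for static positions and withdrawal, and the VR headset is described only for the ETAM tasks. The point does not rest on this.

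**Conclusion.** The point holds as a free improvement. It is not a demonstrated error in the results to come. Randomised order alone does not clear order shifts out of the stated correlations, and adjusting for it is the better method at almost no cost. The possible loss runs from negligible (0.35 to 0.337 at 0.2 SD) to material (0.271 and power 0.780 at 0.5 SD in both blocks). It is minor when one block shifts, and it reverses sign when the shifts oppose each other. These figures rest on reading 0.35 as a correlation, on 1:1 order and on additive shifts. Adjustment restores the within-order correlation fully only if the shifts are additive, which is uncertain for timed tests and scored tasks. The sample size need not change.

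**What to change.** 1. For all participants, compute the MST to MR-MST correlations as partial Pearson correlations given randomised order, or partial rank correlations where Spearman is chosen.
2. Use these adjusted values to decide which pairs go on to regression, and include order as a covariate in those regressions.
3. Report block B and block C means and SDs by order, so that readers can see how large the shifts were.

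The cost is one degree of freedom (power 0.949 to 0.947 if there is no order effect), one covariate and one table. Order comes from the randomisation plan, so no new data are needed and the change also covers participants already tested ("As of July 15, 2022, a total of 70 participants have been screened"). If the full analysis plan already adjusts for order, only the analysis paragraph of the article needs a sentence saying so.

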## Methods

### Study Design, Participants, and Recruitment Procedure

This study developed a protocol for a single-center observational crossover design study. Male and female volunteers (N=100) aged 60 to 75 years were recruited from the pool of participants who had participated in the previous phase of the project. The volunteers were invited to a second visit at the Health Perception Lab, FH JOANNEUM University of Applied Sciences. Assuming that the effects were larger than the previous project phase, an effect size of 0.35 was selected. Therefore, with α=.05 and β=.95, a sample size of approximately 100 participants was considered sufficient for this study. Feasibility reasons and recruitment experience were also considered for the laboratory setting and geographical region. The recruitment and enrolment process for participants with stringent inclusion criteria (ie, age 60-75 years; absence of movement; and visual, auditory, neurocognitive, and psychiatric disorders) lasted from March 2022 to April 2022. For recruitment, participants were contacted by email or telephone to obtain consent and make preliminary agreements for participation. The study procedure, including the application of the respective information and technology devices, was presented to the volunteers. Participants were excluded from the study if they developed 1 or more of the conditions described in Textbox 1.

Study exclusion criteria.Clinical diagnosis of mild cognitive impairment or dementiaClinical diagnosis of mental illness (eg, depression, psychosis)Reduced mobility (eg, walking aid, wheelchair)Aided hearing or visual impairmentParticipation in any other cognitive training study within the last 6 monthsPresent guardianship according to the provisions of the Austrian adult protection law

All selected volunteers are tested once with the MST and once with the MR-MST in a randomized order. An independent investigator executed the randomization plan using a computer-generated random numbers table.

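### Regression is reserved for test pairs whose observed MST to MR-MST correlation is strong, so the same data select and estimate the relation, and poorly tracking pairs get no multivariable analysis

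*Protocol article*

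**What the plan says.** The protocol article, Outcome Parameters and Data Analysis, sets out three layers of analysis for the comparison of the conventional tool (MST) with the mixed-reality tool (MR-MST).

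- Correlations between components: "Spearman rank correlations (Spearman ρ) or product-moment correlations (Pearson correlations) will be calculated, depending on the distribution of the collected data".
- Description: "Descriptive statistics of the data will be presented as means and SDs".
- A conditional third step: "Multiple regression analyses will be conducted for cases of strong effects in the correlation between the MST and MR-enhanced MST".

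The first two carry no condition. The third depends on the size of the correlation seen in the study's own data, and no value is attached to the word *strong*. The significance level is given as "The level of significance is set at α=.05".

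The data are paired: "All selected volunteers are tested once with the MST and once with the MR-MST in a randomized order". Under Strengths and Limitations the article says that the study was designed to compare the two blocks. It expects the modes may not be directly comparable and adds: "These findings will shed more light on the extent, art, and origin of possible differences". The same section lists learning from the first block, fatigue, time of day and investigator as possible influences on results.

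**The concern.** Two things follow from the rule as written.

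First, it selects and estimates on the same sample. A pair whose correlation is high partly by chance is more likely to be taken into regression, and the regression then reports that same chance excess as part of the relation.

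Second, multiple regression is the only multivariable method the article names. Where the MR version ranks participants differently from the conventional version, a model with order and participant characteristics could help to explain why. Under the rule, those pairs do not get one.

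At stake is how far the regression results can be trusted as evidence that an MR test can stand in for its conventional counterpart, and whether the study can say much about the source of discordance where discordance is greatest.

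**Working it through.** **Inputs.** From Study Design, Participants, and Recruitment Procedure: "an effect size of 0.35 was selected" and "with α=.05 and β=.95, a sample size of approximately 100 participants was considered sufficient for this study". The metric of the effect size is not named, and the stated β is workable only as power. The cut-off for *strong* is not in the article; 0.5, 0.6 and 0.7 are assumed here as a range.

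**Step 1: the plan's own figure.** Reading 0.35 as a correlation, two-sided α = 0.05, power 0.95, by Fisher z:

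n = ((1.960 + 1.645) / atanh(0.35))² + 3 = (3.605 / 0.3654)² + 3 = 100.3, so 101.

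This matches the stated figure of about 100. Other readings fit less well: a one-sided correlation test needs 85, a paired standardized difference of 0.35 needs 107 to 109, and a regression f² of 0.35 needs 40 to 80 for 1 to 10 predictors. A correlation of 0.35 is therefore a plausible planning value, but this is an inference.

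**Step 2: how often a pair passes the gate.** With true correlation ρ and cut-off c at N = 100:

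P(r ≥ c) ≈ 1 − Φ((atanh c − atanh ρ) × √97).

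For ρ = 0.35 and c = 0.5: (0.5493 − 0.3654) × 9.849 = 1.81, giving about 3.5%. For ρ = 0.40: (0.5493 − 0.4236) × 9.849 = 1.24, giving about 11%.

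**Step 3: what the selected pairs show.** The table uses 200,000 simulated sample correlations per value (bivariate normal, N = 100). Each gated cell gives the share passing |r| ≥ c and the mean r among those that pass.

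| True ρ | Mean r, no gate | c = 0.5 | c = 0.6 | c = 0.7 |
|---|---|---|---|---|
| 0.35 | 0.348 | 3.6%; 0.529 | 0.07%; 0.617 | practically none |
| 0.40 | 0.399 | 11%; 0.535 | 0.4%; 0.620 | practically none |
| 0.50 | 0.498 | 51%; 0.557 | 8.2%; 0.628 | 0.1%; 0.714 |
| 0.60 | 0.598 | 93%; 0.609 | 51%; 0.649 | 4.6%; 0.720 |
| 0.70 | 0.698 | 99.9%; 0.698 | 96%; 0.703 | 51%; 0.738 |
| 0.80 | 0.799 | 100%; 0.799 | 100%; 0.799 | 99%; 0.800 |

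Without the gate the correlations are essentially unbiased. With it, the overstatement at true 0.50 is about 0.06, 0.13 and 0.21 for cut-offs 0.5, 0.6 and 0.7. Once the true value is 0.1 or more above the cut-off, the overstatement is about 0.01 or less. At true 0.35 and cut-off 0.5, the mean r² among selected pairs is 0.28, against a true 0.35² = 0.12.

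**Step 4: from correlation to regression.** With the counterpart score as sole predictor, the standardized slope equals r, so the overstatement carries over directly. With further covariates its size cannot be derived, because the article does not give the model.

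**Step 5: does the gate track differences between modes?** Adding a constant of one SD to one of two scores correlated at 0.80 leaves the correlation at 0.80. A test that is uniformly slower in MR but preserves ranking passes the gate; one with equal means but disturbed ranking fails it.

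**The case against.** The strongest reply is that the rule concerns a follow-up step and does less harm than it first appears to.

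- A reader might infer that weakly correlated tests go unanalysed. They do not: correlations, means and SDs are planned without condition.
- A reader might infer that all reported relations are inflated. Nothing says that weak correlations will be withheld, and the full set is essentially unbiased. Only the regressed subset is affected.
- A reader might infer that the gate shuts out exactly the tests where the modes differ, and so runs opposite to the aim. Step 5 shows otherwise: correlation is blind to a shift in level, so the gate does not sort tests by that kind of difference.
- A reader might infer that a test behaving as planned would almost never be modelled. That needs 0.35 to be a correlation and the cut-off to be 0.5 or higher; the article states neither.
- The pairs are the same test in two formats. The article cites test-retest values of 0.82 for the Match 4 Point Test and 0.78 for the ETAM. These are not cross-mode correlations, but true values well above a cut-off of 0.5 cannot be excluded, and there the inflation vanishes.
- Nor is false discovery of a relation the issue: with no true correlation, |r| ≥ 0.5 at N = 100 arises less than once in a million.
- The usability work (video observation, questionnaires, cognitive walkthrough) also bears on where differences come from, though in a small sample.
- The cut-off and the model terms may stand in a fuller document that is not shown.

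All of this stands as a limit on size and wording. It does not remove the core. The article states the rule itself, and any cut-off applied to the observed correlation, wherever it is defined, would still select and estimate on the same data. Nor does the usability work adjust test scores for order or participant factors.

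**Conclusion.** The concern holds in limited form. The gate makes the choice of modelled pairs depend on the result, and it overstates the relation in the regressed subset when the true correlation is near or below the cut-off. Under an assumed cut-off of 0.5, bivariate normality and N = 100, the overstatement is about 0.18 at true 0.35 (in the 3.6% of studies where such a pair passes), 0.06 at true 0.50, and essentially nil at true 0.70. A stricter cut-off moves the affected range upward.

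Separately, and without depending on any cut-off value, pairs with poor agreement in ranking are denied the one named multivariable analysis, while a strong correlation gives no assurance that the modes agree in level. The gate is thus a poor guide to where an explanation is needed. The documents do not support the claim that the ungated correlations are biased or that any test is left without analysis. Nor can p-values and intervals be declared invalid across the board for a regression whose outcome and predictors are not given. The wording should be changed before analysis; the article reports that no results were yet available.

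**What to change.** Drop the condition. For every same-test pair in blocks B and C, fit one prespecified model whatever the correlation and report all of them:

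- outcome: the MR minus MST difference where both modes are on the same scale (for example completion times in seconds for the Trail-Making Test), otherwise the MR score regressed on the MST score;
- terms: randomized order of blocks B and C, and a short prespecified list of block A covariates such as age and sex.

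Fix in advance which outcome form applies to which test, so that this does not become a new choice made on the data. If a correlation-gated regression is kept in addition, set its cut-off beforehand and label it exploratory.

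The change affects analysis wording only and uses data the study already plans to collect. The downside is a few more models to report.
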